## Abstract

**Introduction:**

Children and adolescents, diagnosed with cancer, frequently develop physical and cognitive impairments. Hence, cancer and its treatments contribute to reduced physical activity (PA) and cognitive impairments, particularly in executive functions (EFs). Research indicates that PA in school children improves EFs, with cognitively challenging PA offering potential additional benefits. The aim of this study is to investigate the effects of cognitively challenging PA during acute cancer care on cognitive and physical performance, as well as mental health.

**Methods:**

This prospective, two-arm, non-randomized, multicenter controlled study will take place at four pediatric oncology centers in Switzerland. In the intervention group the effect of cognitively challenging PA (*n* = 35) will be compared with standard care plus PA recommendations in the control group (*n* = 35) in newly diagnosed pediatric patients with cancer aged 6-17.99 years. The twelve-week cognitively challenging PA intervention consists of three-weekly 45-minute individualized and supervised sessions incorporating cognitive elements. Assessments of EFs, motor abilities, cardiovascular health, health-related quality of life, fatigue, and physical and psychosocial functioning will be conducted at baseline, six weeks, twelve weeks, and a six month follow-up. All participants in the intervention and control group will receive PA recommendations during the intervention period and an offer for post-therapy PA counseling.

**Discussion:**

Childhood is a crucial period for brain and motor development, rendering young cancer patients especially vulnerable to cognitive and physical impairments from the disease and its treatment. This study is the first to implement cognitively challenging PA tailored to pediatric cancer patients with the aim to enhance EFs by activating brain networks responsible for higher-order processes, physical performance and mental health. The findings will provide insights into the role of cognitively challenging PA and explore its integration into standard care to improve quality of life for childhood cancer survivors.

**Trial registration:**

ClinicalTrials.gov (NCT06839794) and German Clinical Trial Register (DRKS00036573)

## Background

A cancer diagnosis and its treatment in children and adolescents frequently leads to physical impairments such as decline in fitness, muscle loss, and frailty [1, 2]. Over the past decades, the 10-year overall survival rate in high-income countries has significantly improved to 80% [3]. However, this improvement has shifted attention toward the potential long-term impairments associated with the disease, its treatment and the manifested reduced physical activity (PA) [4–6]. 70% of all childhood cancer survivors (CCSs) develop a chronic health condition within 30 years of cancer diagnosis [7]. The most common late effects of CCSs include cardiovascular diseases, hearing loss, renal function impairment, endocrine dysfunctions, hypothyroidism, infertility, as well as neurological and cognitive impairments [8].

Cognitive late effects, including impairments in attention, memory, and processing speed affect around 35–60% of CCSs [9]. Risk factors for cognitive impairments in pediatric cancer patients include high cranial radiation doses, large irradiated brain volume, younger age at diagnosis, and central nervous system (CNS) surgery [9]. These impairments affect particularly higher-order cognitive domains, such as executive functions (EFs) [9], which are required for performing and monitoring goal-oriented, adaptive, and flexible behavior [10]. EFs are essential in unfamiliar, complex, and demanding environments and conditions [10]. One EF model suggests three core processes of EFs (a) inhibition, (b) working memory, and (c) cognitive flexibility, that are important for inhibiting predominant responses and controlling selective attention, for processing and retaining information; and shifting between mental sets and tasks [11]. Additionally, EFs predict a wide range of developmental outcomes (self-control, frustration tolerance, physical health) and academic achievement in children [12, 13].

Apart from these long-term effects, hospitalized children and adolescents often engage in less PA than their healthy peers, spending more time sedentary in bed [5, 14, 15]. Chemotherapy exerts a considerable impact on patients’ activity levels due to its various limiting side effects such as nausea, fatigue, anemia, muscle weakness, and peripheral neuropathy [6, 16]. Consequently, long hospital stays and bed restriction may lead to excessive rest and physical deconditioning [17]. Research shows that, sedentary behavior persists into survivorship [18]. This could contribute to the impaired motor abilities observed in CCSs compared to healthy controls, which are correlated with a lower physical self-concept. Both aspects are linked to health-related quality of life (HrQoL) in CCSs [19]. Taken together, disease, treatment and reduced PA level result in long-term impacts across psychosocial, physical, and cognitive domains [19–23]. Given the significant long-term physical as well as cognitive side effects, there is a pressing need for prevention and early treatment strategies [23].

In recent years, a growing body of evidence highlights the positive impact of PA during acute therapy and PA counseling in aftercare [6, 24–30]. PA has been shown to enhance fitness, sleep, balance, motor abilities, body composition, mobility, HrQoL, and fatigue in children and adolescents with cancer in acute therapy or aftercare [6, 25, 31, 32]. However, empirical evidence is limited when it comes to the effects of PA on cognitive performance during acute therapy. Initial evidence shows that cognitive cancer-related impairment in children after acute cancer care, can be reduced through PA, yielding better cognitive performance than standard care or no intervention [33–35]. CCSs, treated with cranial radiotherapy for a brain tumor performing aerobic exercises, showed alterations in white matter integrity and hippocampal volume and improved reaction time compared to no exercise training in a crossover design [34].

However, specificity of PA interventions is considered an important factor for the benefits of PA for cognitive performance [36, 37]. In recent years, increasing attention has been given to the concept of *cognitive challenge*, defined as the degree of attentional resources and cognitive effort required to master complex tasks [36, 38]. Systematic reviews and meta-analyses indicate that cognitively challenging PA plays a crucial role in enhancing EFs in children and adolescents [39–43]. This is explained by the cognitive stimulation hypothesis [44] suggesting that cognitively challenging PA enhances cognition by activating brain networks involved in higher-order processes [44–46]. Cognitively challenging PA includes for example learning a sequence of movements, where positive feedback can even boost benefits for EFs [38, 47]. Regarding the pediatric oncology field, a feasibility study has explored the effects of sensorimotor training combined with cognitive tasks in pediatric survivors of posterior fossa tumor with positive effects on visual-motor performance [48]. To our knowledge, during acute cancer care, only one study has investigated the effects of combining physical and attentional activities on standardized cognitive performance [49]. However, this study did not include a control group without PA [49]. Showing that, research continues to explore the combination of PA and cognitive tasks to evaluate their potential for more effectively mitigating cognitive impairments [48, 49].

Taken together research is needed on the effects of cognitively challenging PA on both cognitive and physical performance in children and adolescents with cancer undergoing acute treatment. In the present study, we aim to address this while also ensuring that participants continue to receive appropriate support following the PA counseling offered—an element recognized as essential in pediatric oncology care [24]. Additionally, our approach aligns with the recommendations of the International Late Effects of Childhood Cancer Guideline Harmonization Group, which highlights the importance of targeting cognitive functioning and HrQoL in this vulnerable population [33].

### Objectives and hypotheses

The primary objective of this study is to investigate whether a twelve-week cognitively challenging PA intervention in children and adolescents with cancer has a positive effect on their EFs.

Secondary objectives are to investigate whether the twelve-week cognitively challenging PA program has a positive effect on cardiovascular health, motor abilities, body composition, psychosocial functioning, HrQoL and fatigue. Additionally, feasibility, safety, and adverse events of our PA program will be assessed. A PA counseling in maintenance therapy or aftercare will be offered to all participants, and its feasibility will be explored using qualitative interviews.

## Methods

The study is an investigator-initiated, two-phase, non-randomized multicentre controlled trial. During the first phase, the intervention will commence at the Inselspital Bern, while the University Children’s Hospitals Basel and Zurich, as well as the Children’s Hospital Aarau will serve as control sites. In the second phase, after 1.5 years, the intervention will be implemented in Basel, Zurich and Aarau, with Bern serving as the control. Due to ethical considerations, randomization of participants within a single center was not feasible; therefore, the control group consists of participants from other centers.

### Participants

In total, a minimum of 70 participants (for details, see sample size calculations), will be included, with 35 assigned to the intervention (IG) and 35 to the control group (CG).

Children and adolescents aged 6–17 years with a diagnosis of any type of cancer requiring chemo- and/or radiotherapy, expected to last a minimum of at least six weeks at the time of recruitment, and/or CNS surgery, will be included.

Participants will be excluded if they have cognitive and physical disabilities (e.g. down syndrome, cerebral palsy), that prevent participation in the intervention. Additionally, the inability to follow the procedures of the study, e.g. due to language problems, is an exclusion criterion.

### Recruitment

Patients will be screened for eligibility according to the inclusion and exclusion criteria and recruited by a study investigator or treating physician. No additional screening procedures are required beyond verifying inclusion and exclusion criteria. As this is a two-phase study, enrolment into the IG and CG is timely and locally determined.

No monetary compensation will be provided to study participants. However, small thank-you gifts and vouchers will be given as a token of appreciation for participation.

### Intervention for IG

The intervention is based on the “S2k Guideline: Promotion of Exercise and Exercise Therapy in Pediatric Oncology”, the international Pediatric Oncology Exercise Guidelines [1, 50] and findings and experience from our previous cognitively challenging PA intervention studies [51–54]. The intervention consists of cognitively challenging PA designed for children and adolescents undergoing acute cancer treatment (Table 1).

**Table 1 Tab1:** Design of the cognitively challenging PA session during acute therapy

Elements of PA session	Time (minutes)	Content
Welcome	3	State of health and overview of the PA session
Warm-up	5	Opening ritual or game
Cognitively challenging PA	5	PA incorporating cognitive challenges focusing on EFs
Individualized PA	5–30	Strength, endurance, coordination, flexibility, relaxation, balance, cognition
Cool-down	3	Closing ritual or game, e.g. short breath exercises
Reflection and goodbye	2	PA diary

*EFs* Executive functions, *PA* Physical activity

The entire intervention is designed to be playful, and physically, and cognitively challenging. The intervention will be conducted over a twelve-week period, during which the participants will engage in supervised training sessions of 45 minutes, three times a week. The timing, frequency and intensity will be adjusted to accommodate each child’s and adolescent’s current health and fitness status as well as individual abilities. This adaptive approach prevents overexertion and ensures that all participants can actively engage while being optimally challenged. Each PA session follows a structured format: 1. warm-up phase, 2. cognitively challenging PA task, 3. multimodal PA elements designed to train functional mobility, cardiopulmonary fitness, and muscle strength [1]. Examples of the PA elements are listed below:

– Warm-up: PA games, as holding a balloon high– Cognitively challenging PA: Each exercise session incorporates cognitively challenging PA, targeting EFs such as inhibition, cognitive flexibility, and working memory. A representative example is the stop-dance activity, where participants must abruptly stop moving when the music ceases. An extension is that the children are required to execute specific stopping actions in response to predetermined commands.– Strength: Strengthening exercises utilizing small equipment (e.g., weights, books, mini-bands), such as performing glute bridges with mini-bands around the legs.– Endurance: Activities including jumping, running, and dancing, integrated into endurance-based games such as walking memory.

At the end of each session, participants complete an exercise diary, in which the training session is summarized. To minimize drop-out rates after temporary or permanent discharge from hospital, a similar online program will be offered to the participants in the IG. This digital alternative will allow them to maintain engagement in PA, ensuring continuity of the intervention even outside the hospital setting.

### Intervention for CG and IG

#### PA recommendations

All children and adolescents will receive general PA recommendations (based on the above-mentioned guidelines) following the baseline measurement. After the twelve-week measurement (T2), participant will receive individualized PA recommendations in the form of a personalized letter. This letter provides information on the patient’s performance during a motor ability test (Moon test; see Measurements) and offers recommendations for improving motor abilities through age-appropriate PA tasks.

#### PA counseling

In addition, to support long-term PA engagement, all participants in maintenance therapy and aftercare will receive a PA counseling. This will consist of two to four guided counseling sessions aimed to assist reintegrate children and adolescents into local sports club, school sport and leisure-time activities. The counseling sessions will take place, when maintenance therapy starts. During the counseling, the patient’s individual motives for exercise and sport will be addressed, and matching activities will be identified [55, 56]. This personalized approach allows for determining feasible and beneficial PA for the patient [55].

### Study procedure and measurement time points

Participants will be enrolled in the study within the first three weeks after their cancer diagnosis. Subsequently to study inclusion, the baseline measurement will be conducted (T0). Afterwards, children in the IG will participate in a twelve-week cognitively challenging PA program. After six weeks, an interim measurement (T1) is carried out for both groups and again after twelve weeks at the end of the intervention (T2). To record possible long-term effects of the intervention, a follow-up measurement is carried out after six months (T3). At each of these four predefined and above-described measurement time points, all assessments will be conducted during a routine outpatient visit and/or during hospitalization (Fig. 1).

**Fig. 1 Fig1:**
[figure not shown]
Study design and measurements. CG = Control group, IG = Intervention group, PA = Physical activity

### Outcome measures

To avoid carry over effects from physical to cognitive assessments, physical performance assessments will be placed at the end. For each participant, the assessment will be as follows: Body composition, assessment of EFs, cardiovascular measurements except endurance measurement, motor ability related measurements and the 6 min-Walking-Test at the end. The questionnaires are distributed last.

#### Executive Functions (EFs)

The following table provides a summary of three cognitive function tests, detailing their primary purpose, task procedure, duration, target age group, and key outcome measures. These tests assess the three core EFs, including inhibition, cognitive flexibility and working memory. They have been validated across different age ranges. (Table 2). 

**Table 2 Tab2:** Summary of the primary outcome measurements (EFs)

Test Name	Cognitive Function Assessed	Task Description	Duration (minutes)	Age Range (years)	Outcome Measures	Reliability	Ref.
Hearts and Flowers Task	Inhibition and cognitive flexibility	Participants sit facing a screen and respond by pressing a button on the corresponding side when a heart stimulus appears and on the opposite side when a flower stimulus is displayed. Three blocks: congruent (hearts), incongruent (flowers), and mixed (both).	5	4–45	Reaction time, accuracy, composite score	Cronbach’s alpha = 0.83 Test-retest reliability: 0.62 for accuracy score 0.72 for reaction time	[10, 57–61]
Fish Flanker Task	Inhibition	Participants sit in front of a screen and respond to the orientation of a central fish while ignoring surrounding fish, which may show in congruent or incongruent directions.	8	6–18	Reaction time, accuracy, composite score	ICC = 0.92	[62, 63]
Digital Corsi Block Task	Visuospatial working memory	Participants replicate sequences of illuminated blocks on a digital screen, with increasing sequence length in case of correct responses.	varies	>7	Block span, total correct sequences, summary score	ICC = 0.93 for children, ICC = 0.76 for adolescents	[64–69]

*ICC* Intraclass correlation coefficient

#### Self-regulation, cardiovascular health, body composition, motor abilities, PA levels, HrQoL and others

The following table summarizes various health assessments used to evaluate self-regulation, cardiovascular health, body composition, motor abilities, PA levels, HrQoL, fatigue, physical self-concept, PA enjoyment, body image and frailty in children and adolescents, particularly in the context of cancer therapy. Each assessment’s focus, methodology, duration, target age group, and key outcome measures are outlined (Table 3).

**Table 3 Tab3:** Summary of the secondary outcome measures

Secondary Outcomes	Measurement Focus	Methodology	Age Range	Outcome Measure	Reliability and Validity	Ref.
Self-Regulation	Self-Regulation	Head-Toes-Knees-Shoulder Task: Participants follow commands with rule-based changes (e.g., ‘If I touch my foot, you touch your head’), with increasing complexity over time.	3 to 68.55 years	Correct responses	Test-retest reliability (*r* = 0.60–0.66) Construct validity (*r*_*s*_ = 0.46–0.56)	[70–74]
Cardiovascular Health	HRV	Chest belt (EcgMove 4)	Children and adolescents undergoing cancer therapy	HRV		[75–80]
	Aortic stiffness	Mobil-O-Graph		PWV		
	6MWT	6 min walking distance		6MWT distance	Test-retest ICC = 0.944, correlation with VO2max (*r* = 0.61)	
Body Composition	Body fat percentage, skeletal muscle mass	BIA after fasting for eight hours	Children and adolescents undergoing cancer therapy	Body fat percentage, skeletal muscle mass	Utilized in pediatric cancer patients	[81–85]
	Skinfold thickness	Caliper		Triceps skinfold thickness	Validated in pediatric cancer patients	
Motor Abilities	Strength, speed, coordination, flexibility	MOON test with seven items: pin insertion, static stance, reaction time, sit-and-reach, medicine ball throw, stand-and-reach, hand grip strength	4 to 18 years (normative data: 6 to 17 years)	Performance on MOON test	Feasibility established in pediatric cancer patients	[86–89]
	Postural control	Bilateral- (EC), semitandem- (EO) and unilateral (EO) stand	Children and adolescents undergoing cancer therapy (5 to 18 years)	Centre of pressure measured by a force plate (Leonardo, Novotec, Pforzheim, Germany)		
PA Levels	Self-reported PA levels	Questionnaire: BSA	Children and adolescents	Last 4 weeks of sporting activity: 6 items	PA correlation with anaerobic threshold (*r* = 0.27–0.35)	[90–94]
	PA intensity	Questionnaire: GSLTPAQ (abbreviated German-language version)		Light, moderate, and vigorous PA levels: 3 items	Modified version: test-retest reliability of *r* = 0.68	
HrQoL and Fatigue	Physical, emotional, social, and academic functioning	Questionnaire: PedsQL Generic Core (physical, emotional, social, academic)	5 to 18 years	Scores: PedsQL Generic Core: 23 items	Reliability (Cronbach’s α = 0.88–0.93) Construct validity confirmed	[95–97]
	Fatigue	Questionnaire: PedsQL Multidimensional Fatigue Scale		Scores: Multidimensional Fatigue Scale: 18 items	Reliability (Cronbach’s α = 0.89–0.92) Construct validity confirmed	
Physical Self-Concept	Coordination, strength, flexibility, endurance, and the two global scales: physical self-concept and self-esteem	Questionnaire: PSDQ-S for ages 11–17	8 to 17 years	Scores: 22 items	Reliability (Cronbach’s α = 0.79–0.90)	[98–101]
		Questionnaire: PSQC-C for ages 8–12		Scores: 15 items	Reliability (Cronbach’s α = 0.77–0.90)	
PA Enjoyment	Enjoyment of PA	Questionnaire: Short version of PACES-S	11 to 17 years	Scores: 4 items	Test-retest reliability (*r* = 0.76) Internal consistency (Cronbach’s α = 0.87)	[102, 103]
Body Image	Appreciation of body function	Questionnaire: German FAS	Children and adolescents	Scores: 7 items	Reliability (Cronbach’s α = 0.88), Moderate validity (*r* = 0.65, *p* < 0.05)	[104, 105]
Frailty		Series of five measurements: weakness (hand strength), slowness (6MWT), shrinkage (triceps skinfold), exhaustion (PedsQL multidimensional fatigue scale), PA (BSA, GSLTPAQ)	Children and adolscents	Frailty Score		[84]

*BIA* Bioimpedance analysis, *BSA* [Bewegungs- und Sportaktivität Fragebogen] Physical activity and sports questionnaire, *EC* Eyes closed, *EO* Eyes open, *FAS* Functionality Appreciation Scale, *GSLTPAQ* Godin-Shephard Leisure-Time Physical Activity Questionnaire, *HRV* Heart rate variability, *HrQoL* Health-related quality of life, *PA* Physical activity, *PACES-S* Physical Activity Enjoyment Scale – short version, *PSQC-C* Physical Self-Description Questionnaire for Children, *PSDQ-S* Physical Self-Description Questionnaire – short version, *PWV* Pulse-wave velocity, *Ref* Reference, *6MWT* 6 Minute Walking Test

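### At T0 the four-week BSA activity recall mixes time before and after diagnosis in a share that varies by child, while the T1–T3 recalls are wholly post-diagnosis

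*Protocol article*

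**What the plan says.** - **Enrolment and T0** (Study procedure and measurement time points): "Participants will be enrolled in the study within the first three weeks after their cancer diagnosis". The baseline measurement follows inclusion; no maximum gap between the two is given.
- **Schedule** (same section): T1 comes after six weeks, T2 after twelve weeks, and T3 is a six-month follow-up. "At each of these four predefined and above-described measurement time points, all assessments will be conducted during a routine outpatient visit and/or during hospitalization". The BSA is therefore given at T0 as well as later.
- **Instrument** (Table 3, PA Levels): the BSA outcome is "Last 4 weeks of sporting activity: 6 items". The second activity questionnaire, the GSLTPAQ, is described as "Light, moderate, and vigorous PA levels: 3 items", with no recall period.
- **Frailty** (Table 3): five components, of which activity is one; it draws on the BSA and the GSLTPAQ.
- **Analysis** (Statistical analysis plan): for primary and secondary outcomes the within factor is time point, with levels T0 to T3. Linear mixed models replace the ANOVA if they converge. They adjust for potential baseline imbalances and use each child's own interval in days, introduced because the periods between waves will differ.
- **Allocation** (Methods; Recruitment): by centre and phase, with Bern and the other three centres exchanging roles after 1.5 years.

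**The concern.** The recall period is longer than the enrolment window. A BSA completed soon after diagnosis therefore asks partly about life before diagnosis, and how much depends on the day T0 took place. From T1 on, the same question covers post-diagnosis time only. The repeated-measures or trajectory model nevertheless treats the four values as one quantity measured four times.

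The Background gives reason to expect a gap between the two periods: "hospitalized children and adolescents often engage in less PA than their healthy peers, spending more time sedentary in bed". If activity drops around diagnosis, a T0-to-T1 fall will appear in both arms even if nothing changes between those two visits, and its size will vary with the timing of T0. If one arm is tested later after diagnosis than the other, some of that fall would appear as a group-by-time difference.

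**Working it through.** The plan gives no figure of its own on this point. Its sample size concerns the primary outcomes and is not involved.

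**Inputs.** Recall window 28 days (Table 3). Enrolment 0 to 21 days after diagnosis, T0 afterwards with no stated limit, T1 and T2 at 42 and 84 days, counted here from T0 (Study procedure and measurement time points). Let d be the days from diagnosis to T0.

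**1. Pre-diagnosis share of the T0 recall** = max(0, 28 − d) / 28.

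| d (days) | Pre-diagnosis days | Share |
|---|---|---|
| 0 | 28 | 100% |
| 7 | 21 | 75% |
| 14 | 14 | 50% |
| 21 | 7 | 25% |
| 24 | 4 | 14% |
| 28 or later | 0 | 0% |

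The last day with any pre-diagnosis time is day 27 (28 − 27 = 1 day). If d is uniform over 0–21 (assumption), the mean share is 1 − 10.5/28 = 62.5%.

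**2. Later waves.** The T1 recall runs from 42 − 28 = 14 to 42 days after T0, and the T2 recall from 84 − 28 = 56 to 84 days after T0. Both lie wholly after diagnosis for every d ≥ 0, and T3 is later still. Only T0 is mixed.

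**3. Effect on the T0-to-T1 change.** Assume that the score averages activity linearly over the window, with level 100 before diagnosis and a constant 50 after it. The T0 value is (100 × (28 − d) + 50 × d) / 28, which gives 100, 87.5, 75 and 62.5 for d = 0, 7, 14 and 21. T1 is 50 in every case. The apparent fall is 50, 37.5, 25 and 12.5, although behaviour does not change after diagnosis. With post-diagnosis levels of 25 or 0 instead, T0 at day 21 is 43.8 or 25.

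**4. Noise.** For d uniform over 0–21 the standard deviation is 21/√12 = 6.06 days. The T0 value therefore varies between children, through timing alone, by 6.06/28 = 22% of the pre/post gap (one standard deviation).

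**5. Difference between arms.** While T0 falls within 28 days of diagnosis, a difference of Δ days in mean lag moves the T0 contrast by Δ/28 of the gap. Seven days gives 7/28 = 25%, that is 12.5, 18.75 or 25 points for the assumed falls from 100 to 50, 25 or 0. The documents report no such difference.

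**6. Offset from the role swap.** Suppose Bern has mean lag L_B and the other centres L_O, both stable over time. Let Bern supply a fraction p of the intervention arm and q of the control arm. Then Δ = (p − q)(L_B − L_O). This is zero if p = q, and equals the whole centre difference only if the swap contributed no children (p = 1, q = 0).

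**The case against.** **Bias between arms.** A reader might infer that, because arms are formed by centre, a centre difference in lag must bias the group comparison. The Methods section does not support that. Every centre is planned to serve in both roles, so a stable difference tends to cancel. Residual bias needs unequal recruitment across phases or a lag that drifts over time. The design allows both, but the documents show neither.

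**Every child.** A reader might also infer that every T0 recall reaches before diagnosis. The three-week limit applies to enrolment, not to T0, and a T0 on day 28 or later contains no pre-diagnosis days. This limits the wording but widens the mixture to 0–100%. Nor can the earlier time be called healthy: a child may already be ill before diagnosis. Later waves cannot be called treated time either, since eligibility asks only for therapy expected to last at least six weeks and/or CNS surgery.

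**The model already adjusts.** The mixed model lists time and the group-by-time interaction with no group main effect, which reads as a baseline-adjusted model. This removes much of the harm of an ordinary change score. It does not address the lag: the individual time variable is introduced for the intervals between waves, and the characteristics named for the comparability checks do not include it. If lag shifts T0 BSA, adjusting for T0 BSA alone carries part of that shift into the follow-up contrast.

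**Frailty.** It would be too strong to say that the T0 frailty score is invalid. Activity is one component of five, it also draws on the GSLTPAQ, and the rule for combining components is not shown. Removing the BSA at T0 alone would make the score differ in construction between waves, which is the same fault in another form.

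**Conclusion.** The point holds and is minor. The documents fix the recall length, the enrolment window, the schedule and the role of T0 in the analysis. Together these make T0 BSA a child-specific mixture (25–100% pre-diagnosis for T0 on days 0–21, falling to none from day 28) that is not the same quantity as BSA at T1–T3. Part of the T0-to-T1 change is then a product of the recall window, and timing adds noise.

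The shares follow from the stated windows alone. The activity levels, the uniform lag and linear averaging of the score are assumptions, so the point sizes are illustrative. Bias in the group comparison is conditional on an undocumented lag difference between arms.

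The reach is the BSA outcome and one frailty component. Both stand in Table 3, though neither is named among the secondary objectives. The point is shown only for the BSA, because the GSLTPAQ recall period is not given. The primary executive-function outcomes are untouched.

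**What to change.** - Derive days from diagnosis to T0 for each child and compare it between arms with the other baseline characteristics.
- Base the BSA group comparison on T1–T3, with T0 BSA and this lag as covariates.
- Describe T0 BSA in reports as mixed pre-/post-diagnosis activity.
- Keep the frailty score constructed identically at all four waves and adjust it for the same lag. Add a sensitivity analysis that omits the BSA item at every wave.

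**Cost.** One derived variable and a few sentences of analysis text. The diagnosis date has to be known anyway to apply the three-week enrolment limit. No visit, questionnaire or participant burden is added. The loss is the change-from-baseline reading of BSA, which the recall window already compromises.
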